### Analysis

The targeted clinical outcome (VOZZ suicidal behaviors) will be evaluated in agreement with the intention-to-treat principle using linear mixed modeling with VOZZ at baseline as covariate. Reporting of the results will be conducted in accordance with the CONSORT statement [52].

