### Design

The presented study is designed as a non-blinded cluster-randomized controlled trial with two parallel groups (experimental and control) to evaluate the effectiveness of a multimodal stepped-prevention program relative to (enhanced) usual care. The participants in the experimental condition will receive all four modules of the multimodal stepped-prevention program, whereas participants in the control condition will receive modules 1 and 2. Randomization will be conducted at school level (to be more precise: at the level of school location because one school can have annexes at multiple locations) to avoid contamination. An independent statistician will randomly assign the participating school locations to the intervention or control condition using random.org. Furthermore, randomization will be stratified for (1) education level (vocational training as one category, in Dutch: VMBO; and higher education / pre-university as the other category, in Dutch: HAVO/VWO) because school type is a relevant prognostic predictor of outcome [54]. Like most psychological and public health interventions, blinding of participants is not possible; therefore, it will not be attempted. The assessments will be conducted at baseline (T0), during the intervention phase after the third module (T1), at post-intervention (T2), at 6-month follow-up (T3), at 12-month follow-up (T4), and at 24-month follow-up (T5). The overall study design is shown in Fig. 1.

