### Sample size

We powered our study to detect a standardized mean difference *d* = 0.38 (or larger) on the central clinical outcome (suicidal behaviors) using a test for independent means at α = 0.05 (2-tailed) and power of (1-b) = 0.80 while considering the design effect of the cluster randomization with schools as the unit of randomization and students being nested within schools. The relevant parameters are (1) the intraclass correlation coefficient, rho; the mean cluster size, *m*; the coefficient of variation, *cv*, of the cluster sizes; and the minimally detectable effect size, *d*. Regarding the last parameter, we looked at the well-known SEYLE study [55], where 2764 pupils in 43 schools were randomized to a universal prevention consisting of a Youth Aware of Mental Health (YAM) program (comparable to our universal intervention) and compared to a control group of 2933 students in 40 schools. YAM was associated with a significant reduction in incident suicide attempts (OR = 0.45, *p* = 0.014) and a reduction in severe suicidal ideation (OR = 0.50, *p* = 0.025). In our study, we expect similar or better effects because in addition to the universal preventive module, we will also offer the safety net provided by the gatekeepers training in addition to early detection and referral for adolescent students at elevated risk of suicide. For screen-positive students, an additional indicated preventive module will be offered. Nonetheless, we conservatively assume that the effectiveness of our integrated multi-component intervention will be of equal effectiveness as the YAM program. The OR of 0.50 translates into a standardized mean difference, *d*, of 0.38 when the outcome is measured on a continuous scale, as we will do [56]. The mean cluster size of *m* = 215 will be based on student population in the previous year. In the last year, the smallest school had 74 students and the largest 340. Accordingly, it follows that coefficient of variation *cv* = 0.31 [57]. In the SEYLE study of Wasserman et al. [55], the intraclass correlation coefficient was estimated at rho = 0.01 for severe suicidal ideation. To obtain an estimate of the required sample size, we used Stata’s procedure to estimate sample size needed for an independent groups t-test in a cluster randomized trial [58]. The corresponding syntax of clustersampsi, samplesize mu1(0.00) mu2(0.38) sd1(1) sd2(1) rho(0.01) m(215) size_cv(0.31) indicated *n* = 645 per condition, or *n* = 1290 in both trial arms. We will also compensate for a maximum of 30% dropout, which implies that we will need to have 1290/(1–0.30) =1844 participants at baseline.

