#### Evaluation of secondary outcome

The intervention’s effect on the secondary outcome (CDI-2 depression) will be investigated in the same way as the primary outcome (VOZZ suicidal behaviors); hence, using linear mixed modeling with baseline CDI-2 depression as a covariate.

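### The VOZZ and CDI-2 models do not name the education-level stratum used in the randomisation, which costs precision if that factor is as prognostic as the protocol says

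*Protocol article*

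**What the plan says.** Under Design, the protocol article allocates school locations to two arms and states that "randomization will be stratified for (1) education level", with vocational training as one category and higher or pre-university education as the other. The reason given is "because school type is a relevant prognostic predictor of outcome".

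Under Analysis, the primary outcome is to be evaluated by intention to treat, "using linear mixed modeling with VOZZ at baseline as covariate". Under Evaluation of secondary outcome, CDI-2 follows the same form, "using linear mixed modeling with baseline CDI-2 depression as a covariate". Neither sentence names education level.

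Under Other study parameters, demographic variables, baseline VOZZ and baseline CDI-2 are compared between arms, and any variable that differs becomes a covariate in every effectiveness model.

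Under Sample size, the design values are "α = 0.05 (2-tailed) and power of (1-b) = 0.80" with the syntax terms "mu1(0.00) mu2(0.38) sd1(1) sd2(1) rho(0.01) m(215) size_cv(0.31". The calculation "indicated *n* = 645 per condition, or *n* = 1290 in both trial arms", and the dropout allowance gives "1290/(1–0.30) =1844 participants at baseline".

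**The concern.** The design and the analysis do not match. The design controls a factor at randomisation because it predicts outcome, but the model lists its covariate and omits that factor. Stratifying balances the factor between arms. The analysis collects the gain in precision only if the model also removes the factor's variance from the error term. Otherwise the standard error is estimated as though that variance still added to the difference between arms.

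The imbalance rule does not close the gap. It acts on observed differences, which stratification is meant to prevent, so it tends to leave out the one factor the design calls prognostic. Chance differences in pupil numbers could still bring education in, and the primary model would then depend on the data.

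This matters more than usual because there are few schools. Precision is set at school level, and every school-level degree of freedom counts, both for and against adjusting.

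**Working it through.** **Reproducing the plan's figures.** For two means with d = 0.38, SD 1, two-sided 5% and 80% power, n = 2(1.96 + 0.84)²/0.38² = 108.7 per arm. The design effect for unequal clusters is DE = 1 + [(cv² + 1)m − 1]ρ = 1 + (1.0961 × 215 − 1) × 0.01 = 3.347. The product, 108.7 × 3.347 = 364, is 1.69 schools of 215, rounded up to 2. One further school per arm, a usual small-sample allowance, gives 3 × 215 = 645, as stated. Without it the result is 430, which does not match. For dropout, 645/0.70 rounds up to 922 per arm, and 2 × 922 = 1844.

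**Implied number of schools.** 1290/215 = 6 and 1844/215 = 8.6, so about 6 to 9. This is inferred from the mean cluster size; the article does not state it.

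**Effect of naming the stratum.** The variance of a school mean is V = DE/m, the standard error with k schools per arm is √(2V/k), and the degrees of freedom are 2k − 2. If education explains a share q of between-school variance, naming it replaces ρ by ρ(1 − q) and leaves 2k − 3 degrees of freedom. The share q is an assumption; ρ = 0.01 and cv = 0.31 come from the article.

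- Three schools of 215 per arm, stratum omitted: V = 3.347/215 = 0.01557, SE = 0.102, d/SE = 3.73, power 79% on 4 df.
- Same, named with q = 0.5: V = [1 + (1.0961 × 215 − 1) × 0.005]/215 = 0.01011, a 35% cut.
- Four schools per arm, with 215 × 0.70 = 150.5 pupils each: V falls from 0.01754 to 0.01209 at q = 0.5, a 31% cut.

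Power from the non-central t distribution:

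| Schools per arm | Stratum omitted | Named, q = 0 | Named, q = 0.25 | Named, q = 0.5 |
|---|---|---|---|---|
| 3 of 215 | 79% | 70% | 77% | 86% |
| 4 of 150.5 | 92% | 90% | 94% | 97% |

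Leaving out the cv term gives the same pattern: 82% against 73%, 80% and 87% for three per arm, and 93% against 91%, 95% and 98% (97.5% before rounding) for four.

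**Direction of the error.** School means were simulated with stratified allocation (strata of 4 and 2 schools, or 4 and 4) and a REML fit, with 2,500 runs per null setting and 1,500 per power setting. With education explaining half of between-school variance and left out of the model, a t-test on school degrees of freedom has size 0.7% to 1.6% for ρ of 0.01 to 0.05, below the nominal 5%. With six schools and ρ = 0.01, the mean standard error is 0.103 with the stratum omitted and 0.080 with it named, and power is 76% against 84%. With eight schools and ρ = 0.05, a value not in the article, power is 39% against 69%.

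**Reference distribution.** If a normal-based test were used without the stratum in the model, its analytic size would be 12.2% on 4 df, 9.8% on 6 df and 9.1% on 7 df. In the simulation with a non-prognostic stratum and ρ = 0.01 it was 10.2% with six schools and 8.7% with eight. A t-test on school degrees of freedom stayed at 3.4% to 5.0% for ρ of 0.01 to 0.05.

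**The case against.** The strongest reply is that the omission makes no statement false and leaves the test valid, and that a fuller analysis plan may name the stratum. It is also fair to say that the article does not restrict the model to the baseline score: educational background is listed in the Background among the socio-demographic factors, so the imbalance rule could admit it, and with schools of 74 to 340 pupils balanced strata of schools do not guarantee balanced pupils. This stands as a limit on the wording. The article names only the baseline score; it does not exclude education. But a rule driven by observed imbalance does not replace fixing a design factor in advance.

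The gain is also uncertain. The share q has no source in the article, and baseline VOZZ, already in the model, may absorb part of a stable education difference, so q must be read as what remains after it. The lost degree of freedom is one of four with six schools. All of this stands and is why the size is given as a range that includes losses.

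A reader might go further and infer that, with so few schools, the reported p-value will be about twice as liberal as stated. The documents do not support that. The article says only that a linear mixed model will be used and chooses no normal-based test; degrees of freedom are commonly left to the full protocol or analysis plan; and the 645 is reproduced only with an extra school per arm, which suggests that small numbers were considered. Omitting a prognostic stratum also works in the opposite direction, towards conservatism.

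**Conclusion.** The mismatch is real and worth correcting: the factor called prognostic under Design is absent from both specified models. The consequence is lost precision and a conservative test, not a false-positive risk. At ρ = 0.01 and d = 0.38, with education explaining a quarter to half of between-school variance, naming it changes power by about +1 to +5 points with four schools per arm. With three per arm the range is from about −2 points to a gain of about 5 to 8, the upper end coming from the simulation. If education explains nothing, the cost is about 2 or 9 points respectively. The article's own claim that school type is prognostic favours including it. These figures rest on the assumed variance share, the inferred number of schools, and strata split evenly between arms. They concern VOZZ only, since the article gives no sizing values for CDI-2.

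The choice of degrees of freedom is a linked point to clarify and not an error in the text.

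**What to change.** Under Analysis and Evaluation of secondary outcome, name the education-level stratum as a pre-specified fixed effect beside arm and the baseline score, whatever balance is observed, with a random intercept for school location. State that the 12-month contrast is tested with Kenward-Roger or Satterthwaite degrees of freedom, or point to where the full plan says so; a normal-based test with this many schools would run at about 9% to 12%.

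The change is one of wording and needs no extra participants. It costs one school-level degree of freedom, which matters most if only six schools take part, so the number of schools should be stated too.

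A stratified school-level permutation test is not a useful check at these numbers. Six schools split 4/2 allow 6 × 2 = 12 allocations, so the smallest two-sided p is 2/12 = 0.17. Eight split 4/4 allow 6 × 6 = 36, giving 2/36 = 0.056. Neither can reach 0.05.

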#### Evaluation of secondary outcome

The intervention’s effect on the secondary outcome (CDI-2 depression) will be investigated in the same way as the primary outcome (VOZZ suicidal behaviors); hence, using linear mixed modeling with baseline CDI-2 depression as a covariate.

#### Analysis of effect mediation

It is important to determine the mediators that affect the intervention effect. This helps determine whether the intervention works through expected mechanisms and which improvements could be effective. Mediation analyses will be performed in Mplus [73], where indirect effects will be tested with bootstrap methods. More specifically, we will test whether (1) mastery, (2) stigma, (3) worry, (4) top problems, (5) social connectedness, and (6) hopelessness will mediate the intervention effect on VOZZ suicidal behaviors and / or CDI-2 depression.

Increased awareness through stigma reduction will be the main intervention target of the universal prevention. We hypothesize that reduction in stigma will also reduce suicidal behaviors and depressive symptomatology and mediate the effect of the intervention. Moreover, stigma is also related to social isolation, which is another important risk factor for suicidal behaviors [74]. Research has found that people often withdraw from social life due to fear of rejection as a result of stigmatizing attitudes towards mental health problems [75, 76]. Hence, reduced stigma is likely to reduce social isolation. Previous research has also shown that students who have negative attitudes towards school and thus feel less connected to the school are at an increased risk for suicide attempts [77]. School-based programs are expected to induce attitude changes in school staff and students. Moreover, group-based interventions could reduce the feeling among adolescents that they are the only ones experiencing depression, which is often associated with adolescent depression, as youngsters often do not share depressive feelings with each other due to fear of stigmatization. Furthermore, social isolation can also reduce treatment response [78]. In line with this, studies have shown that each social group that a depressed individual joins decreases relapse rates in depressed individuals and results in a more pronounced improvement on depressive complaints [79]. Thus, social connectedness is an interesting factor to examine as a potential moderator considering both depression and suicide prevention. Both the interpersonal theory [80] and the integrated-motivational-volitional model [81] theorize that reduced social connectedness increases suicidal ideation through the sense of thwarted belongingness. Christensen [82] found that mastery is also related to the sense of thwarted belongingness and in accordance with previous research, the researcher has found that lower levels of mastery are significantly associated with suicide ideation [83]. In theory, mastery ensures that people have the ability to manage negative experiences [84]. Those who feel lack of control (i.e., mastery) over situations are more likely to turn to suicidal ideation, much like a self-fulfilling prophecy. Moreover, suicidal ideation may give people a false sense of mastery when they feel they lack mastery naturally [85].

In addition to social connectedness and mastery, repetitive thinking is also suggested as a mechanism affecting depression and suicidal ideation [86]. Research has found that repetitive thinking predicts not only presence of depression and suicidal ideation, but also their duration [87, 88]. Furthermore, repetitive thinking decelerates the recovery after the treatment [89–91]. In line with this, Kerkhof and van Spijker [92] identified worrying (i.e., repetitive thinking) as a proximal risk factor of suicidal behaviors. Interestingly, mastery has been associated with negative effect of repetitive thinking [93], which may also be an important mediator, as mentioned before. Another interesting finding is that hopelessness may partially mediate the relationship between repetitive thinking and suicidal ideation [94]. Hopelessness has also often been named as one of the most important predictors of suicide attempts and behaviors [95–98]. Moreover, it is considered to mediate the relationship between depression and suicidal behaviors [95]. Perfectionism is often related to the feelings of hopelessness [99]. Just like those with lower levels of mastery, a person with high feelings of perfectionism may be more likely to turn to suicidal ideation in line of negative events or feelings of hopelessness [100, 101]. As opposed to mastery, perfectionism is traditionally viewed as a more stable trait [102]. Thus, we hypothesize that perfectionism may moderate rather than mediate the treatment outcome. In addition, it is also important to record life events, as they can increase the risk of depressive symptomatology [103]. Negative life events are also associated with the occurrence of suicidal ideation [97]. However, the most important variable is the experienced disruptiveness of life events. As such, recurrences in depression are often associated with negative life events due to kindling and sensitization [104–106]. We expect that the multimodal stepped-prevention program will also reduce the disruptiveness of life events and in turn decrease occurrence of depressive symptoms.

#### Explorative analysis of effect moderation

Finally, moderation analyses will be conducted to determine which adolescents benefit most from the intervention. Additionally, it will help determine whether some adolescents would be better served by receiving adapted or other interventions. We will conduct a series of a priori planned moderator analyses to see whether the intervention effect is moderated (increased or diminished) by the following moderators: (1) gender, (2) ethnic descent / cultural background, (3) level of baseline perfectionism, (4) level of baseline VOZZ suicidal behaviors, and (5) level of baseline CDI-2 depression. We call these analyses explorative because the data-analytical strategies will be non-parametric in nature, such as bootstrap-aggregated CART analysis and random forest methods implemented in the R statistical package.

Several socio-demographic factors have been found to affect suicide and depression prevention. Previous research has found that gender may play an important role in CBT-based programs. Age has also been found to influence treatment outcome in depression prevention studies. Girls and older participants were found to experience more beneficial effects of interventions. It is also important to consider ethnic and cultural background. It has been well established that ethnicity influences help-seeking behaviors and the ways in which suicidal behaviors or depressive symptoms are expressed [107]. Hence, ethnicity might in turn also influence the perception and integration of treatment.

#### Other study parameters

Possible baseline imbalances between the two conditions in demographic variables, VOZZ suicidal behaviors, and CDI-2 depression will be verified. If any variables show different distributions across the two conditions, they will be entered as covariates in all models testing the effectiveness of the intervention.

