The identification of and subsequent intervention for those with elevated signs of depressive symptomatology should also be important components of the prevention of suicidal behaviors [21]. Cognitive behavioral therapy (CBT) is an effective treatment for depression, and many indicated prevention programs are based on CBT, such as ‘Op Volle Kracht (On Full Power: OVK). OVK was modeled after the Penn Resiliency Program (PRP) [49]. The program successfully reduced depressive symptoms in adolescent girls with subclinical depressive symptoms [50]. A modified OVK version (OVK2.0) by de Jonge-Heesen, et al. [51] will be implemented and investigated at schools with adolescents who have been identified as scoring higher on depressive symptoms, as measured by self-report.

The primary aim of our study will be to investigate the effectiveness of a multimodal stepped-prevention program to reduce suicidal behaviors and depressive symptoms. We hypothesize that suicidal behaviors will decline as a result of a multimodal preventive intervention relative to care as usual enhanced with screening and the gatekeepers’ safety net. Since most modules of the stepped-prevention program are based on depression prevention program, we expect that depressive symptoms will decline as well. Secondary aims are to investigate the mechanisms of change by studying the effect mediators and moderators. Previous research has identified several factors that contribute to lower treatment response in depression and suicidal behaviors. Socio-demographic factors, such as age, gender, cultural background/ethnicity, and educational background, have been found to moderate treatment outcome. Therefore, their effects will be examined. Other factors that could influence treatment outcome are perfectionism, hopelessness, and baseline depressive symptoms and suicidal behaviors. Furthermore, other factors that are related to the proposed prevention modules could mediate outcome, such as stigma, social connectedness, mastery, worry, and life events. We hypothesize that the factors that impede treatment response will have a similar effect on the outcomes of the multimodal stepped prevention program.

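### Beyond the fixed baseline outcome, covariates are chosen by observed arm differences with no stated criterion, a rule that tends to leave out the prognostic stratification factor

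*Protocol article*

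**What the plan says.** The Analysis section of the protocol article evaluates the primary outcome "using linear mixed modeling with VOZZ at baseline as covariate". The section on the secondary outcome treats depression in the same way, "using linear mixed modeling with baseline CDI-2 depression as a covariate". These two covariates are fixed.

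The section on other study parameters then adds a check: "Possible baseline imbalances between the two conditions in demographic variables, VOZZ suicidal behaviors, and CDI-2 depression will be verified". Its consequence, for every model of the intervention's effectiveness, is: "If any variables show different distributions across the two conditions, they will be entered as covariates in all models". It does not say what counts as a difference, whether students or schools are compared, or which demographic variables are meant. The Background names candidates: "Socio-demographic factors, such as age, gender, cultural background/ethnicity, and educational background, have been found to moderate treatment outcome".

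On allocation, the Design section states "Randomization will be conducted at school level" and that "randomization will be stratified for (1) education level". The reason it gives is that school type is a relevant prognostic predictor of outcome. The analysis sections do not name education level as a covariate. Under Recruitment, students are informed and give consent after their school has been randomized.

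**The concern.** A covariate earns its place by predicting the outcome. The size of its observed difference between arms is a poor guide to that. A rule driven by imbalance can admit a weak predictor that happens to differ and leave out a strong one that happens to balance.

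Here the rule works against the design. Education level was chosen for stratification because it is prognostic. Stratification makes it similar across arms, so the check is unlikely to select it. The between-strata variation then stays in the school-level residual, although the design has already removed it from the arm comparison. The estimate is as precise as the design made it, but the reported standard error is too large and power is lost.

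The missing criterion also matters. Two analysts who both follow the text could fit different primary models, and one of them may choose after seeing the baseline data by arm in a non-blinded trial.

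**Working it through.** **Inputs.** From the Sample size section: d = 0.38, SD = 1, rho = 0.01, mean cluster size m = 215, cv = 0.31, two-sided alpha 0.05, 80% power, 645 per arm, 1844 at baseline. The rule itself comes with no figure.

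**The plan's own sample size.**
- Design effect: 1 + [(1 + 0.31²) × 215 − 1] × 0.01 = 3.35.
- The stated 645 per arm is 645/215 = 3 schools per arm. A t-based cluster calculation with 2 × (3 − 1) = 4 degrees of freedom gives 79.4% power, so the figure reproduces to within rounding.
- The baseline total implies 1844/215 = 8.6, so about nine schools. I therefore use four per arm for the stratum check, two in each education stratum.

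**How often the check flags a chance difference.** The criterion is not stated, so two readings are shown. The number of candidates is assumed. Four are age, gender, ethnicity and CDI-2. Six adds education level and VOZZ. They are taken as independent, with rho = 0.01 for all, although the document gives that value only for severe suicidal ideation.
- *Student-level 5% tests ignoring clustering.* Per variable: 2 × [1 − Φ(1.96/√3.35)] = 0.284. At least one of four: 1 − 0.716⁴ = 0.74. At least one of six: 1 − 0.716⁶ = 0.87. Simulation with 3 + 3 schools of varying size gives 73% and 85%, and 4 + 5 schools gives the same. At an assumed ICC of 0.05 the figures are 96% and 99%.
- *5% tests on school means.* 1 − 0.95⁴ = 0.19 and 1 − 0.95⁶ = 0.26, whatever the ICC. Simulation agrees.
- For the primary model, four is the more relevant count. VOZZ is already in that model, and education level is stratified.

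**What is lost when the stratum is left out.** Assume that the two education strata differ by 0.2 SD in the outcome after baseline adjustment. The document gives no figure. Four schools per arm, two per stratum, are analysed on school means.
- Variance of a school mean: 0.01 + 0.99/215 = 0.0146. True standard error of the arm difference: √(2 × 0.0146/4) = 0.085.
- Without the stratum, each school lies 0.1 SD from its arm's mean because of its stratum. This adds 8 × 0.1² = 0.08 to the residual sum of squares, or 0.08/6 = 0.0133 to the residual variance. That becomes 0.0279, and the estimated standard error is about √(2 × 0.0279/4) = 0.118.
- The ratio is 0.118/0.085 = 1.38, so the standard error is overstated by nearly 40%.
- Simulated results:

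| Model | Type I error | Power at d = 0.38 |
|---|---|---|
| Stratum left out | 1.2% | 81% |
| Stratum included | 4.9% | 94% |

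**The case against.** The strongest case against the point has five parts.

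1. *Inflated error was not shown.* A simulation of the worst-case reading used student-level 5% tests on four independent covariates, 3 or 5 schools of 215 per arm, ICC 0.01 or 0.05, and assumed standardized slopes of 0.1 to 0.3. Type I error under the rule was 4.1–5.3%, against 4.4–5.4% with all four always adjusted. There was no bias, and the standard deviation of the estimate was within about 1.5% of full adjustment. This stands: a reader might infer that nominal error rates break down, and nothing supports that. The simulation did not include the stratification factor, however, which is where the loss arises.
2. *The check is informative here.* Students consent after schools are randomized, in a non-blinded trial, so a difference may reflect selective consent and need not be pure chance. This stands, and is why the check is kept as a sensitivity analysis. It also favours fixed adjustment, which does not wait for a difference to be detected.
3. *The rule need not trigger often.* A reader might infer that, with few schools, it almost always will. The documents do not support this, because they give no criterion. The driver is ignoring clustering with large schools; moving from six to nine schools hardly changes the student-level rate.
4. *There is no contradiction with the Analysis section.* That is right. The rule supplements that model and makes it provisional. The primary model is also not wholly data-driven, since baseline VOZZ is always in it.
5. *An analysis plan not shown may define the criterion.* It may. Any definition would still select covariates by imbalance, and that rule is stated here.

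**Conclusion.** The point holds in limited form. The article states a rule under which every covariate beyond the baseline outcome depends on observed arm differences, by a criterion it does not give. The main cost is the likely omission of education level, which the article itself calls prognostic.

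Under the stated assumptions (0.2 SD stratum effect, 4 schools per arm, rho = 0.01, school-level analysis), that omission makes the test conservative, with type I error about 1%, and takes power from about 94% to about 81%. The loss shrinks with a weaker stratum effect and vanishes if there is none.

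False flags are likely if the check ignores clustering: about 28% per variable, and 73–85% for at least one of 4 to 6. They are much less likely, at 19–26%, if it is done on school means. Correlation between the variables would lower the figures for at least one flag somewhat. ICCs for demographics and CDI-2 are not in the document.

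**What to change.** Replace the rule with a short covariate list fixed in advance for all effectiveness models:
- the baseline value of the outcome (already fixed);
- the education-level stratum;
- a few prognostic student-level variables, such as gender, age and baseline CDI-2.

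Describe baseline characteristics by arm without significance tests. Keep adjustment for observed imbalance only as a labelled sensitivity analysis, which remains useful because consent follows school randomization.

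The cost is one paragraph. No new data are needed, and the sample sizes of 1290 and 1844 do not change. The one downside is that the stratum uses a between-school degree of freedom. With four schools per arm, 6 becomes 5 and the critical t value rises from 2.45 to 2.57, a small power loss if education level turns out not to be prognostic. For the same reason, school-level covariates beyond the stratum should be avoided.
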